# Efficacy and safety of the orthopaedic manipulation techniques of the Lin School of Lingnan Region in the treatment of adolescent idiopathic scoliosis: protocol of a participant-and-assessor-blinded randomized controlled study

**DOI:** 10.1186/s12891-023-07152-9

**Published:** 2024-01-04

**Keywords:** Scoliosis, Spinal curvature, Spinal diseases, Bone diseases, Musculoskeletal diseases, Manipulation

## Abstract

**Background:**

Adolescent idiopathic scoliosis (AIS) is the most common developmental spine disorder among children. It is characterized by a lateral deviation of the spine that gives rise to the distinctive “S” or “C” shaped bending of the spine. The Lin School of Lingnan Region (LSLR), one of the prominent schools for bare-handed orthopaedic manipulation in southern China, provides preliminary evidences that the orthopaedic manipulation techniques help to correct deviations of the spine. Previous research found that Orthopaedic Manipulation Techniques of LSLR (OMT-LSLR) could reduce the Cobb’s angles in patients with AIS. Therefore, the current study aims to investigate the effectiveness and safety of the OMT-LSLR in treating teenagers with AIS.

**Methods:**

In this participant-and-assessor-blinded randomized controlled clinical trial, 50 participants identified AIS without surgical indications will be recruited and randomized into two groups to receive physiotherapy scoliosis-specific exercises training with either orthopaedic manipulation or sham manipulation treatment for 16 weeks, followed by post-treatment visits at week 24. Primary outcome measure is the change of Scoliosis Research Society-22 (SRS-22) questionnaire score. Secondary outcome measures include Traditional Chinese version of Spinal Appearance Questionnaire (TC-SAQ) score, Italian Spine Youth Quality of Life (ISYQOL) score, the change of Cobb’s angle measured by Xray, and the change of Cobb’s angle, spinal rotation and muscle volume measured by three-dimensional (3D) ultrasound. The trial will be conducted at the Chinese University of Hong Kong Chinese Medicine Specialty Clinic cum Clinical Teaching and Research Centre in Hong Kong (CUHK-CMSCTRC).

**Discussion:**

The results of this study will establish comprehensive clinical evidence about the efficacy and safety of the Orthopaedic Manipulation Techniques of the Lin School of Lingnan Region in the Treatment of Adolescent Idiopathic Scoliosis. One of the characteristics of this trial is that it is a participant-and-assessor-blinded randomized controlled clinical trial with sham manipulation. The study would also apply three-dimensional (3D) ultrasound technology to investigate the relationship between the change of the muscle volume and the spinal curve.

**Trial registration:**

The trial is registered on ClinicalTrials.gov (Identifier: NCT05639023) on December 6, 2022.

## Background

Adolescent idiopathic scoliosis (AIS) is the most common developmental spine disorder among children. It is characterised by a lateral deviation of the spine, with a Cobb’s angle of more than 10 degrees, that gives rise to the distinctive “S” or “C” shaped bending of the spine [1, 2]. According to the World Health Organisation (WHO), it is estimated that 2,000 to 3,000 children aged between 13 and 16 suffer from AIS for every 100,000 adolescents in the world [3]. In China, study found that the overall scoliosis prevalence rate was 5.14% [4] In Hong Kong, the incidence of AIS is reported to be approximately 3.5%, and it is anticipated to increase progressively in the foreseeable future [5]. AIS does not only influence patients’ appearance, but also increases their risk of back pain and sports injuries, as well as affects their normal growth and development [6, 7]. Consequently, these may have a negative impact on their quality of life [8, 9]. For severe cases, the patients might even suffer from chronic pain or impaired cardiopulmonary function [10–12]. At present, the treatment available for AIS include both operative and non-operative options, and they will be prescribed according to the severity of the spinal deformity. As recommended by the Scoliosis Research Society (SRS), operative treatment is indicated for patients with Cobb’s angle greater than 45 degrees [13, 14]. For Cobb’s angle less than 45 degrees, non-operative interventions such as scoliosis bracing and physiotherapy scoliosis-specific exercises (PSSE) are usually considered for patients [15]. Despite having available treatment for AIS, there are still limitations, with the surgical approach having inherent risks and non-operative approaches lacking desirable evidence for the therapeutic outcomes [15–18].

From the perspective of Chinese medicine (CM), AIS is a spinal disorder that can be treated by CM orthopaedic manipulation. Among different orthopaedic manipulation, the Orthopaedic Manipulation Techniques of the Lin School of Lingnan Region (OMT-LSLR) is one of the prominent schools for bare-handed orthopaedic manipulation in southern China [19]. In a clinical case report [20], the combination of Lin School manipulation techniques and exercise interventions showed a decline in Cobb’s angles among patients with AIS. These results may be promising, but they are at most preliminary evidence and further research is definitely warranted for a comprehensive assessment.

This clinical study aims to examine the clinical efficacy and safety of the OMT-LSLR in the treatment of Adolescent Idiopathic Scoliosis. A randomized controlled trial (RCT) with the treatment duration of 16 weeks and post-treatment follow-up period of 8 weeks was carried out. In this study, we will use comprehensive outcome measures such as health-related quality of life assessment and radiology imaging to evaluate the treatment response.

X-ray imaging is the mainstay in AIS diagnosis and to rule out any underlying conditions in the spine [21]. However, patients with AIS may be subject to multiple radiology imaging for curve progression monitoring, which causes high cumulative radiation in their bodies. Exposure to ionizing radiation have been shown to increase the risk of developing cancer according to previous retrospective studies [22]. In this study, EOS x-ray imaging is applicated and each image can reduce approximately16–34 times lesser organ dose as compared with the standard digital radiography [23]. Moreover, imaging before and after manipulation is required for investigating the effect of manipulation on spine. In order to reduce risk form the radiation, 3D ultrasound imaging is used for the continuous assessment. Ultrasound imaging is an alternative assessment in AIS patients [24]. Previous studies have proven that ultrasound images perform very good correlations and agreement compare with Xray measurements of the scoliotic curvature [25]. Also, ultrasound imaging can be used to measure the changes in muscle [26]. Thus, it can provide a detailed profile of the change in spine before and after the manipulation.

While health-related quality of life assessment is a patient reported outcome measures which provides subjective outcome measurements., both X-ray and ultrasound in the study provide objective outcome measurements. This clinical study will be able to provide comprehensive clinical evidence on the efficacy of OMT-LSLR in the treatment of Adolescent Idiopathic Scoliosis.

### Objectives and hypothesis

The primary objective of the study is to evaluate the clinical efficacy and safety of the OMT-LSLR in the treatment of AIS. The secondary objective is to determine the association between the change in the muscle volume and the spinal curve before and after every treatment. The hypothesise is that the OMT-LSLR is effective for the treatment of Adolescent Idiopathic Scoliosis which will balance the musculoskeletal difference between both sides of the patient’s back.

## Methods/design

### Study design

This study is a prospective trial in participants with AIS and is a participant-and-assessor-blinded randomized controlled trial with the treatment duration of 16 weeks and post-treatment follow-up period of 8 week. Fifty eligible participants will be randomly divided into two groups: the manipulation techniques group and the control group. The allocation ratio will be 1:1. participants in the former group will receive both OMT-LSLR and PSSE, whereas those in the latter group will receive sham manipulation technique, which is similar to OMT-LSLR without any therapeutic effect, and PSSE.

### Study setting

This study will be conducted in The Chinese University of Hong Kong Chinese Medicine Specialty Clinic cum Clinical Teaching and Research Centre (CUHK-CMSCTRC) on the CUHK campus, Hong Kong. CUHK-CMSCTRC is a Teaching and Research Clinic in the university which offering Chinese Medicine treatment.

### Study population

Participants with AIS will be recruited from CUHK-CMSCTRC. Advertisements include posters in the Chinese Medicine clinics and promotion on internet platforms, such as Facebook, emails, and website will be made to facilitate community recruitment. Besides, articles will be published in local newspapers and magazines as well as organize health promotion talks to augment the participant recruitment process. Potential participants with AIS who meet the eligibility criteria will be recruited.

### Outcomes

The study will be conducted over a period of 24 weeks with the treatment duration of 16 weeks and post-treatment follow-up period of 8 weeks. The primary outcome measurement is the change of Scoliosis Research Society-22 (SRS-22) questionnaire score at week 16 when the treatment is completed. SRS-22 questionnaire [27] is used to primarily assess the function/activity, pain, self-perceived image, mental health, satisfaction with treatment and other health-related quality of life parameters when the participants finished the manipulation treatment. In this study, the validated Chinese version of SRS-22 [28] will be used to assess the effectiveness of the treatment.

There are multiple secondary outcomes, including the change of SRS-22 questionnaire score at week 8 and 24, the change of Traditional Chinese version of Spinal Appearance Questionnaire score (TC-SAQ) and Italian Spine Youth Quality of Life (ISYQOL) at week 8, 16 and 24. Both TC-SAQ and ISYQOL are questionnaires specifically for AIS patients. The former, TC-SAQ [29] is a questionnaire specifically assess the cosmetic perception and have already been demonstrated to be excellent for the assessment of appearance in patients. The latter, ISYQOL [30] is used to evaluate health-related quality of life for AIS patients. In the study, validated Chinese version of both questionnaires will be used to assess the effectiveness of manipulation treatment during the treatment and post-treatment period [31, 32].

Secondary outcomes also include the change of Cobb’s angle measured by Xray at week 16, and the change of Cobb’s angle, spinal rotation and muscle volume measured by 3D ultrasound imaging before and after every manipulation. The paraspinal muscle volume will be estimated by a customized MATLAB program, which multiplies the cross-sectional area of paraspinal muscles on each image by the thickness of each image and the total number of images of the target paraspinal muscle. The lateral curvature of the spine in the coronal plane measured by Cobb’s method on X-ray radiograph is the gold standard for assessing scoliosis [33], In the study, a standing whole-spine PA radiograph will be used for measurement and evaluated before and after the 24-week study period. If the patient has double curves, the major curve will be calculated for analysis. Moreover, before and after every manipulation, Cobb’s angle, spinal rotation and muscle volume along the spine will be measured from 3D ultrasound imaging captured by Scolioscan Air. Scolioscan Air is a validated radiation-free system for scoliosis assessment by using coronal images of spine generated by a 3D ultrasound volume projection imaging method [34, 35].

### Eligibility

#### Inclusion criteria

Participants must meet all the following criteria for inclusion [36]:Adolescents aged between 10 and 18 who can speak and read Chinese.Fulfil the diagnostic criteria of scoliosis, i.e. Cobb’s angle ≥ 10 degree.Risser grade ranging from 0 to 4.Informed consent agreement signed by both participant and their parents/guardians.Able to participate in follow-up assessments.

#### Exclusion criteria

Participants will be excluded if they meet one of the following criteria [36]:History of spine surgery.Cobb’s angle > 45 degrees.Known to have severe respiratory or cardiovascular comorbidities; vertebral tumours and spinal canal abnormalities; Leukaemia, thrombocytopenia and other bleeding disorders.Known to have cognitive impairment.Documented pregnancy.Wearing scoliosis brace within 1 month.Involved in other interventional clinical studies at the same time.Uncooperative during treatmentsBeing assessed by investigators as unsuitable to participate.

### The assessor and therapist

The participants will be assessed by a registered Chinese Medicine Practitioner with certificate of Scolioscan operation and who is blinded to this study. The manipulation techniques will be performed by a Chinese Medicine Practitioner who is an expert in the Orthopaedic Manipulation Techniques of the Lin School of Lingnan Region with more than 10 years’ experience. The participating subject will receive PSSE training by certified physiotherapists in a physiotherapy centre.

### Interventions

Participants will be received either 12 times orthopaedic manipulation or sham treatment for 16 weeks: The schedule will be three times of treatment per month and less than twice a week. For PSSE, participants are encouraged to perform home exercise every day on their own throughout the study. Participants will receive five sessions of intensive supervised training for first two weeks and then one to two sessions trainings per month for the rest, amounting to the total of 14 sessions supervise training throughout the study.

### The orthopaedic manipulation techniques of the Lin School of Lingnan Region

The Orthopaedic Manipulation Techniques include steps as follow [20]. First, a combination of X-ray examination and palpation will be first conducted to locate the apex of curve before the treatment. Second, the participants will be seated on the treatment chair, with both hands placed behind the neck. The operator will stand at the side of concave curvature, with one arm placed anteriorly to the participant’s neck and the hand holding firm on the participant’s shoulder of the opposite side, while the other hand is fixed at the mid-lower section of the apex of curve. The assistant will firmly anchor the lower limbs. Third, the participant will be requested to bend forward, with the apex of the curve as the pivot point of the spine curvature. After that, forces will be applied using the hand that was placed on the opposite shoulder. This in turn allows the participant’s spine to rotate along with the force applied. Until a resistance is encountered during the rotation, an explosive force will be applied to the spine using the hand. If the participant has double scoliotic curve, the treatment will be implemented first on the inferior site then superior, following the steps as described above.

### Sham manipulation techniques

For sham manipulation techniques, participants will be instructed to sit on a treatment chair after palpation. The operator will stand at the side of concave curvature, with an arm placed anteriorly to the participant’s neck and the hand holding firm on the participant’s shoulder of the opposite side, while the other hand is fixed at the mid-lower section of the apex of curve. The assistant will firmly anchor the lower limbs. However, the participant only need to rotate slowly without an external force applied to the spine. After that, the operator will stand on the other side and repeat the movement. These non-therapeutic manipulations were performed outside the spinal column with adequate joint slack and without soft tissue pre-tension so that any therapeutic force would not apply to the spine. Rotations to both sides are applied to ensure a broad non-specific movement, which would not produce any therapeutic effect.

### Physiotherapy scoliosis-specific exercises

PSSE training will be conducted by certified physiotherapists in a physiotherapy centre. First, a physiotherapist will conduct physical examinations including manual muscle strength test of the back, muscle tension checking and joint range of motion measurements. Then, the physiotherapist will provide exercise training to the participants according to the examination results. The exercises will be performed in supine, side-lying, prone, sitting, standing and other functional positions [37]. Physiotherapist will incorporate breathing exercises and tactile feedback to enhance the recruitment of target muscles (including paraspinal muscles, abdominal muscles, hip and gluteal muscles) in the desired movements and postures.

### Prohibited other treatments

In order to minimize the participants receiving additional AIS treatments during the study, the participants need to agree that they will not seek additional AIS treatment when they sign the informed consent form. The involved therapists and research personnel will routinely remind the participants during each treatment session. If any participants indicate that they receive additional AIS treatments, the research personnel will document it and use it as a co-variate in the subsequent data analysis.

### Safety

No serious or catastrophic adverse events in children treated by manual therapy were reported in the clinical studies or systematic review [38]. For adults, adverse events such as bruising, muscle soreness are short-lived and minor after manual therapy, and most will occur within 24 h and resolve within 72 h. The risk of major adverse events is very low [39, 40].

### Strategies to improve adherence

In order to encourage the participants to complete the study, the entire treatment including all the interventions and the assessments will be provided at no cost. Participants will receive subsidy in return by following the protocol and completing the study. They will be closely in touch with the researchers to report their symptoms.

### Sample size estimation

PASS 12.0 was used for the sample size calculation. The Scoliosis Research Society-22 (SRS-22) questionnaire score was chosen as the primary outcome indicator. The minimal clinically important difference of SRS-22 ranges from 0.4–0.7 [41]. The standard deviation was estimated to be 0.45 from previous studies about non-operative treatments in AIS patients [42]. To detect a clinically meaningful different of 0.4 in SRS-22, with 80% power at the 0.05 significance level and an assumed standard deviation of 0.45, 21 cases in each group are required. Allowing for a dropout rate of 20%, a total of 50 participants will be recruited with 25 participants for each group.

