### Statistical analysis

All analyses will be conducted according to the intention-to-treat principle. Descriptive statistics will be computed for each of the analysed variables. The primary efficacy analysis will be done by comparing the two groups with respect to score of SRS-22 at baseline and at 8, 16 and 24 weeks after randomization using analysis of covariance (ANCOVA). A complete-case analysis and a linear mixed model analysis of all available data will then be done as supplementary analyses. Repeated measures ANCOVA will be used to test for group differences in the secondary outcomes, including score of TC-SAQ and ISYQOL and the measurement in spinal imaging with adjustment for relevant baseline covariates. Unauthorized treatment will also be added as a covariate in relevant ANCOVA. All statistical tests will be two-sided, and *p* < 0.05 is considered significant difference. The statistical software of SPSS 23.0 will be used for analysis. Adverse events will be categorized, and the percentage of the mild adverse events and serious adverse events will be documented. Chi-square tests will be used to examine differences in the proportion of total and categories of adverse events within each group.

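### Recruiting 25 per group leaves 20 after 20% dropout, one short of the 21 the protocol requires for 80% power

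*Protocol article*

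**What the plan says.** All the sample size figures are in the protocol article, section Sample size estimation. The target is given as "To detect a clinically meaningful different of 0.4 in SRS-22", "with 80% power at the 0.05 significance level", with "an assumed standard deviation of 0.45". From these inputs the section concludes that "21 cases in each group are required". The next sentence makes the allowance for loss: "Allowing for a dropout rate of 20%, a total of 50 participants will be recruited with 25 participants for each group".

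Three further points come from other sections. The endpoint being powered is continuous; under Outcomes, "The primary outcome measurement is the change of Scoliosis Research Society-22 (SRS-22) questionnaire score at week 16 when the treatment is completed". Under Study design, "The allocation ratio will be 1:1". Under Statistical analysis, "All statistical tests will be two-sided". No other section changes the number recruited or the dropout rate.

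**The concern.** A dropout allowance has one purpose: to leave the required number evaluable if the expected share of participants is lost. Here the required number is 21 per group and the expected loss is 20%, yet one fifth of 25 is 5, which leaves 20. The two adjacent sentences cannot both hold, and no outside figure is needed to see it.

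At stake is the power statement for the primary endpoint. A reader or ethics committee will take the section to mean that the trial has 80% power even if it loses a fifth of its participants. That matters most if the result is inconclusive, because 0.4 is the lower end of the 0.4 to 0.7 range of clinically important differences that the section cites. At the planned dropout, the difference detectable with 80% power lies slightly above that lower end.

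**Working it through.** **Inputs**

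- Difference δ = 0.4, SD σ = 0.45, power 80%, α = 0.05: Sample size estimation.
- Two-sided testing: Statistical analysis.
- Equal allocation: Study design.
- Required number 21 per group, dropout 20%, recruited 25 per group: Sample size estimation.

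**Step 1. Reproduce the 21.** For a two-sample t-test with n per group, the noncentrality parameter is δ / (σ√(2/n)) on 2n − 2 degrees of freedom. Power is the probability that a noncentral t variable falls beyond the two-sided 5% critical value.

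- n = 20: 0.4 / (0.45 × √(2/20)) = 2.811; 38 df, critical value 2.024; power 78.2%.
- n = 21: 0.4 / (0.45 × √(2/21)) = 2.880; 40 df, critical value 2.021; power 80.25%.

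The smallest n that reaches 80% is 21, so the protocol's figure reproduces.

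**Step 2. Check the allowance forwards.** 25 × (1 − 0.20) = 20 evaluable per group, against 21 required.

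**Step 3. Check it backwards.**

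- Per group: 21 / (1 − 0.20) = 26.25, rounded up to 27, or 54 in total.
- On the total: 42 / 0.80 = 52.5, rounded up to 53.
- Multiplying instead of dividing: 21 × 1.20 = 25.2 per group, or 50.4 in total. Rounded down, this matches the stated 25 and 50. The article does not show how it reached 25, so this is an inference.

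Fifty is therefore 3 or 4 participants short of what a 20% allowance needs.

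**Step 4. What the 50 delivers** (unadjusted two-sample t-test)

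| Evaluable per group | Dropout from 25 | Power for 0.4 |
|---|---|---|
| 25 | 0% | 86.8% |
| 21 | 16% | 80.3% |
| 20 | 20% | 78.2% |

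The largest dropout that still leaves 21 is 1 − 21/25 = 16%, or 4 participants per group. With 20 per group, the difference detectable with 80% power is 0.409.

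**The case against.** The strongest reply is that the loss is trivial: one evaluable participant per group and about two percentage points of power. The inputs are less certain than that, since the SD is an estimate from earlier studies and the important difference is a range. This stands, and it limits the weight of the point. It does not make the two sentences agree.

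Second, the 80% is attached to 21 per group, where it is true. It fails only if dropout goes above 16%. This also stands: the error lies in the allowance, not in the calculation of the 21.

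Third, the normal approximation gives n = 2 × (0.45 × (1.96 + 0.84) / 0.4)² ≈ 19.9, so 20 per group with 80.3% power, and 20 / 0.80 is exactly 25. But the protocol states 21, which is the t-test answer. Taking the approximation would make the 21 wrong instead, so the section needs correcting either way.

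Fourth, the primary analysis is ANCOVA. If 0.45 is the SD of the unadjusted score and the model adjusts for baseline, the residual SD is 0.45 × √(1 − r²). At 20 per group, power would then be about 81.9% for r = 0.3 and 88.5% for r = 0.5. These correlations are assumptions. The article gives none, does not say whether 0.45 refers to the score or its change, and claims no such gain in its calculation. The shortfall may well be recovered in practice, but the stated arithmetic does not show it.

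Fifth, the analysis is by intention to treat, and week 8 scores from later dropouts would enter the supplementary mixed model. That could recover some information. Even so, the section itself treats dropouts as lost when it inflates for them, and on that basis its allowance falls short.

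**Conclusion.** The point holds. At the protocol's own 20% dropout, 25 per group leaves 20 evaluable, not the required 21. Power for a 0.4 difference is then 78.2%, and the difference detectable with 80% power is 0.409. Fifty participants cover dropout of up to 16%; covering 20% would take 53 or 54.

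The power figures assume an unadjusted two-sided two-sample t-test, SD 0.45, equal loss in both groups, and no information from participants who drop out. The mismatch between 20 and 21 needs none of these assumptions. This is a small error in a figure the trial relies on. It should be corrected, but it does not threaten the design.

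**What to change.** Keep 50 participants and replace the dropout sentence under Sample size estimation with something like:

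> With 50 randomised, 80% power is retained for up to 16% dropout; at 20% dropout (20 per group) power is 78%, on an unadjusted two-sample basis.

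The cost is one sentence and a slightly less favourable stated figure. Recruitment and analysis do not change, and no extra participants are needed. If the investigators prefer to keep the claim of 80% power at 20% dropout, the recruitment target has to rise to 54 (27 per group).
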